### Study sample size

The main objective of this study is the identification of prognosis factors in terms of treatment efficacy. All the variables of interest represent continuous quantitative variables. Moreover, the distributions of the data for the double IGRA and the immunomonitoring assays are quite asymmetrical requiring non-parametric tests for comparison. For these reasons there is no consensus on the number of participants needed. However, the mean sample size of the studies evaluating biomarkers for TB treatment monitoring recently reviewed by Zimmer et al. was of ~50 patients (8). In addition, reference studies assessing T-cell response in TB patients by immunophenotyping such as Adekambi et al. and Ahmed et al. showed significant T-cell phenotypic changes throughout treatment with cohort of 10 and 39 patients respectively (12, 13). Hence, we expect to include 40 patients presenting active pulmonary TB which is consistent with the number of patients diagnosed yearly in the Infectious Diseases department. We consider that it will allow to obtain statistically significant results. The number of 20 LTBI patients was also chosen according to previous studies (13, 24).

### Statistical methods

The prognostic power of each biomarker will be evaluated separately. Biomarkers associated with evolution will be kept for multivariate logistic regression models. These models will allow the obtention of different scores per patient and the characteristics of a composite test will be assessed by studying ROC (receiver operating characteristic) curves and calculating AUC (area under the curve). Analysis of the ROC curves will allow estimation of sensitivity, specificity and AUC via mean and confidence interval obtained by bootstraps.

We will study the kinetics of the different biomarkers (clinical, transcriptomic, proteic, or phenotypic) to identify the most basic and universal immune signatures associated with different TB stages: LTBI, active TB and cure.

When required, analyses will be based on two-sided p-values, with statistical significance defined by p < 0.05 and conducted with the software R. Finally, considering multivariate analyses, appropriate multiple imputations will be taken into consideration in case of relevant amount of missing values.

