### Variables

The following data will be recorded in an Opti-4TB specific electronic Case Report Form (e-CRF): demographics and comorbidities, TB clinical characteristics including symptoms, localization(s) of the lesions, biological and CT-scan findings, anti-TB regimen, and associated therapies. TB microbiological characteristics will include the type of lineage and species of the *M. tuberculosis complex* and the type of sample from which the pathogen has been isolated along with phenotypic and genotypic drug-resistance profile determination. The latter will be obtained through whole genome sequencing (WGS) of each isolate which will also enable the monitoring of *Mtb* micro-diversity (including antibiotic resistance mutations) emergence within each host throughout the treatment.

The PCR-based transcriptomic assay will measure transcripts expression levels of a 6 gene panel named RISK-6 by quantitative real-time (qRT) PCR at each time point (20). The panel includes the following genes: *GBP2, FCGR1B, SERPING1, TUBGCP6, TRMT2A*, and *SDR39U1*. The RISK6 signature score is based on a calculation algorithm taking as input data the cycle thresholds ratio for 9 different pairs of transcripts.

The proteomic assay will measure cytokines and chemokines concentration levels in plasma at each time point using the Bio-Plex Pro™ Human Cytokine 27-plex Assay (Bio-Rad, USA). Cytokines and chemokines will be measured, after whole blood stimulations with either QuantiFERON-Gold Plus kit or an in-House “Heparin-Binding HaemAgglutinin” (HBHA) antigen (21). The concentration levels of IFN-γ measured in this assay will also serve as reference for a double IGRA assay combining the different stimulations mentioned.

The quantitative and functional characteristics of T-cell subpopulations will be assessed by spectral cytometry (Aurora, Cytek® Biosciences, USA) on fixed cells obtained from blood samples taken at each time point and previously stimulated as above-mentioned. A 30 markers panel will be used to identify and quantify each subtype of T-cells. An equal number of total cell events will be recorded to enable comparison between patients and timepoints.

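### Biomarkers are selected, fitted and scored in the same 40 patients, and a bootstrap of the ROC curve does not remove the resulting optimism in AUC, sensitivity and specificity

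*Protocol article*

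**What the plan says.** The Statistical methods section sets out a sequence. It begins with "The prognostic power of each biomarker will be evaluated separately". Then "Biomarkers associated with evolution will be kept for multivariate logistic regression models". The models give each patient scores, and the composite test built from them is assessed by ROC curves. Last, "Analysis of the ROC curves will allow estimation of sensitivity, specificity and AUC via mean and confidence interval obtained by bootstraps". On significance, the section says that, when required, "analyses will be based on two-sided p-values, with statistical significance defined by p < 0.05". It does not name this as the screening threshold.

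On patients, Study sample size says "Hence, we expect to include 40 patients presenting active pulmonary TB". The 20 people with latent infection are controls and add nothing to prediction of treatment outcome.

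On candidates, the Variables section lists a six-gene score ("The PCR-based transcriptomic assay will measure transcripts expression levels of a 6 gene panel named RISK-6") and plasma proteins measured "using the Bio-Plex Pro™ Human Cytokine 27-plex Assay". It also lists T-cell subsets from a 30-marker panel. Biomarker assays describes five stimulation conditions: NIL, TB1, TB2, mitogen and HBHA. NIL and mitogen are the negative and positive controls. All assays are repeated at four visits.

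The Discussion accepts that the many variables may cost power for this sample size. It defers validation to a later multicentre cohort.

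**The concern.** Choosing markers because they are associated with outcome, and then measuring discrimination in the same patients, uses the data twice. The apparent AUC rewards chance associations found at the selection step. Resampling the finished ROC curve shows how that AUC varies from sample to sample. It does not show how much of it came from selection and fitting.

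The abstract's primary objective is to assess how well new biomarkers predict TB outcome. AUC, sensitivity and specificity are the only performance measures that Statistical methods names. If they are optimistic, a set of unrelated markers could be reported as a signature with an interval that excludes 0.5. The Discussion treats the number of variables as a threat to power. The larger risk runs the other way, towards false apparent performance.

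**Working it through.** **Plan's own figure.** There is none to reproduce. The 40 rests on precedent and recruitment, and no target AUC, event rate or number of candidates is stated.

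**Inputs from the article.** 40 TB patients; 27 analytes; 5 stimulation conditions, of which 3 are antigen conditions; one RISK-6 score; 30 cytometry markers.

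**Assumptions, not in the article.** Screening at two-sided p<0.05; 4 to 20 unfavourable outcomes of 40; one visit's readouts; correlation between markers of 0 to 0.3.

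**Candidate counts.**
- RISK-6 plus one 27-plex panel: 1 + 27 = 28
- the same plus 30 cytometry markers: 1 + 27 + 30 = 58
- cytokines in the three antigen conditions: 27 × 3 = 81
- cytokines in all five conditions: 27 × 5 = 135
- everything at one visit: 1 + 135 + 30 = 166

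**Step 1: how many noise markers pass.** With m independent noise markers, the expected number passing is 0.05m, and the chance that at least one passes is 1 − 0.95^m.

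| m | expected to pass | chance at least one passes |
|---|---|---|
| 28 | 1.4 | 0.76 |
| 58 | 2.9 | 0.95 |
| 81 | 4.05 | 0.98 |
| 135 | 6.75 | above 0.99 |

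**Step 2: apparent AUC under pure noise.** This was simulated: 40 patients, Gaussian noise markers, rank-sum screen, all survivors in a logistic model, AUC in the same 40. The ranges are mean AUCs over the assumptions above, among runs in which at least one marker passes.

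| m | mean apparent AUC | true AUC |
|---|---|---|
| 28 | about 0.75-0.91 | 0.50 |
| 58 | about 0.78-0.94 | 0.50 |
| 81 | about 0.80-0.96 | 0.50 |
| 135 | about 0.85-0.99 | 0.50 |

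The upper ends belong to few events and uncorrelated markers, the lower ends to balanced outcomes and correlation 0.3. A cap on model size helps only in part. With 8 or 12 events and at most three uncorrelated markers kept, the mean is 0.83-0.87 for 58 candidates and 0.89-0.93 for 166. A short candidate list reduces the problem but does not remove it. With 10 candidates the mean is 0.72-0.87, and nothing passes in about 60% of runs.

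**Step 3: what the bootstrap adds.** Resampling the final ROC with scores held fixed returns the apparent AUC to within 0.002. Its lower 95% limit exceeds 0.5 in about 93% or more of the runs with 28 to 135 candidates.

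**Step 4: which repair works.** Under the same null, with 8 or 12 events and uncorrelated markers, mean AUC is:

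| Method | 58 candidates | 166 candidates |
|---|---|---|
| optimism correction, only the selected markers refitted | 0.79-0.82 | 0.92-0.96 |
| optimism correction, screening repeated inside | 0.65-0.68 | 0.84-0.87 |
| 4-fold cross-validation, screening inside each fold | 0.47-0.51 | 0.48-0.55 |

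Only scoring of left-out patients, with selection inside, returns about 0.50.

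**The case against.** The strongest reply is that the article condenses a fuller plan. It does not say whether selection is repeated inside the bootstrap, and internal validation is often left to an analysis plan. This is fair as far as it goes: the text does not rule out a sound procedure. But it is not merely silent. It states outcome-driven selection, fitting, scoring and ROC analysis in order, and attaches the bootstrap to the last step. An analyst who follows that order gets a biased answer.

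A second reply is that this is a declared proof of concept with external validation to come. That softens the consequence. It does not correct the AUC, sensitivity and specificity that this study will report, and a noise signature could be carried forward. The article does not, however, call the AUC the basis for the multicentre study. It says that study will test and validate the signatures.

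Several stronger readings are tempting and not supported:
- **An AUC near 0.9 whatever the truth.** The value depends on the event rate, screening rule and candidate count, none of which is stated.
- **135 candidates as a fact.** That count includes the two control tubes. Without them it is 81, and the article does not say which readouts are screened.
- **Few unfavourable outcomes and almost certain separation.** The outcome is a composite of clinical, CT and culture status judged at each visit, so early non-response need not be rare.
- **An unpenalised model.** The article does not say whether the regression is penalised.
- **A bootstrap more optimistic than the apparent AUC.** Resampling the final ROC matches the apparent value and does not exceed it.

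**Conclusion.** The concern holds as a bias in the stated sequence. Selection, fitting and scoring share the same 40 patients, and the bootstrap as described measures spread without removing optimism. Under the assumptions listed, noise alone gives a mean apparent AUC between about 0.75 and 0.99 when any marker passes the screen. Where in that range it falls depends mainly on the number of candidates and the outcome split. The inflation persists with outcomes split 20 to 20.

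The direction of the bias follows from the sequence itself, while its size rests on inputs the article does not supply. The figures describe the case in which every marker is noise. They do not show that the study's markers are uninformative.

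**What to change.** In Statistical methods, state that screening, model fitting and any choice of cut-off are repeated within every resample or fold, with the patient as the unit and stratification by outcome. State also that AUC, sensitivity and specificity come from patients not used for selection or fitting, and label in-sample values as apparent. Refitting only the markers already selected, or applying ordinary optimism correction, should not be accepted as a substitute.

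Repeated cross-validation serves this purpose. Out-of-bag scoring also serves, but if events are few its predictions should be pooled across resamples. With 4 events and outcome-stratified resampling, 4!/4^4 = 24/256 = 9.4% of resamples leave no out-of-bag event, and 144/256 = 56% leave exactly one.

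Penalised regression, and RISK-6 as a comparator that needs no fitting, are useful options but not part of the correction.

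The cost is wording, some extra code, a lower reported AUC and a wider interval. No patient, sample or visit is added.

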## Methods and analysis

### Study design

The Opti-4TB protocol is a single center prospective “proof-of-concept” cohort study of adult patients treated for drug-susceptible (DS) pulmonary TB at the Infectious Disease Department of a 5362 tertiary care university hospital (Lyon, France). Over the past decade, an average of 30 to 50 patients with culture-confirmed TB were diagnosed and treated yearly in the department.

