### Setting

Eligible DS pulmonary TB adult hospitalized for receiving treatment will be assessed for inclusion in the Opti-4TB protocol. The recruitment period will be of 36 months and the patient overall follow-up will be of 6 months covering a total period of 42 months. A control group of 20 LTBI participants will be included.

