### Endpoints

To address the objectives mentioned above, the primary endpoint will be to evaluate the concordance of the kinetics of the biomarkers with the outcome of treated TB patients at each visit. It is a composite outcome including clinical status, radiological computed tomography (CT)-scan assessment and mycobacterial culture conversion of sputum samples.

This will comprise:

1) A whole blood transcriptomic signature based on levels of expression of a panel of 6 genes;2) A proteomic signature based on levels of various cytokines and chemokines production measured in plasma;3) A dynamic phenotypic monitoring of circulating T cell subpopulations through spectral cytometry using a panel of 30 markers;

Secondary endpoints will be to identify profiles, based on the above biomarkers, consistent with three *Mtb* infection stages: LTBI, active TB and cured TB.

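### The bootstrap intervals fixed for sensitivity and specificity have zero width or under-cover when an outcome class is small or accuracy is close to 1

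*Protocol article*

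**What the plan says.** The protocol article, Statistical methods, first evaluates biomarkers one by one. Those associated with evolution go into multivariable logistic models, and the resulting scores are assessed by ROC curves. For the accuracy measures it then fixes one method: "Analysis of the ROC curves will allow estimation of sensitivity, specificity and AUC via mean and confidence interval obtained by bootstraps". The type of bootstrap, the interval level, the number of resamples, stratification and refitting are not given. The only stated error rate is in the same section: "analyses will be based on two-sided p-values, with statistical significance defined by p < 0.05".

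On numbers, Study sample size says "we expect to include 40 patients presenting active pulmonary TB", and Setting says "A control group of 20 LTBI participants will be included". Study design describes "adult patients treated for drug-susceptible (DS) pulmonary TB". No expected number of unfavourable outcomes appears anywhere.

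The outcome to be predicted belongs to the TB patients under treatment and is judged visit by visit. The Endpoints section defines it thus: "It is a composite outcome including clinical status, radiological computed tomography (CT)-scan assessment and mycobacterial culture conversion of sputum samples". The LTBI group enters only through the secondary part of that section, where the stages are latent infection, active disease and cure: "Secondary endpoints will be to identify profiles, based on the above biomarkers, consistent with three".

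**The concern.** A bootstrap can only rearrange the patients who were observed. If a class holds few patients and none is misclassified, no resample can contain a misclassified one, and the interval shrinks to a point. If one or two are misclassified, the resamples still represent the unseen tail poorly. The interval is therefore shortest when the data are scarcest and the result looks best. This happens even with a score defined in advance, such as RISK-6, at a fixed cut-off, so it is a separate matter from overfitting.

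The bootstrap mean adds nothing as an estimate. With a fixed rule, each resampled proportion has expectation x/m, the observed value, so averaging resamples returns that value plus simulation noise.

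The accuracy estimates are how the composite test is to be judged, and the Discussion says a multicentre cohort will follow. A reported sensitivity of 100% with limits of 100% and 100% from a handful of patients would suggest a precision that the study does not have.

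**Working it through.** **The plan's own figure.** The article gives no interval width, power, expected accuracy or event count. The 40 + 20 is justified by earlier studies and yearly recruitment, so there is no precision figure to reproduce.

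**Inputs.**
- TB patients: 40 (Study sample size). LTBI controls: 20 (Setting).
- Interval level: 95%, assumed from the two-sided 0.05.
- Bootstrap type: percentile, with a fixed test rule (assumed).
- Unfavourable outcomes: not stated; 4 to 12 of 40 assumed (10% to 30%).
- True sensitivity or specificity: 0.80, 0.90 and 0.95 (assumed).

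**Method.** If x of m class members are classified correctly, the resampled proportion follows Binomial(m, x/m)/m, and the percentile limits are its 2.5% and 97.5% quantiles. Coverage is the sum, over x, of the Binomial(m, p) probabilities for which the limits contain the true p. No simulation is needed.

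**One cell by hand: m = 4, p = 0.90.**
- x = 4 (probability 0.9^4 = 0.6561): limits 1 to 1, which miss 0.90.
- x = 3 (probability 0.2916): limits 0.25 to 1, which cover.
- x = 2 (probability 0.0486): limits 0 to 1, which cover.
- x = 1 or 0: upper limits 0.75 and 0, which miss.
- Coverage = 0.2916 + 0.0486 = 0.340. The chance of a zero-width interval at 100% is 0.656.

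**All cells (nominal 95%).** The zero-width column is p^m.

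| Class size m | p = 0.90: bootstrap | zero width | Wilson | p = 0.80: bootstrap | zero width | Wilson |
|---|---|---|---|---|---|---|
| 4 | 34% | 66% | 95% | 56% | 41% | 97% |
| 6 | 45% | 53% | 98% | 72% | 26% | 98% |
| 8 | 53% | 43% | 96% | 82% | 17% | 94% |
| 12 | 71% | 28% | 97% | 91% | 7% | 98% |
| 20 | 88% | 12% | 96% | 92% | 1% | 96% |
| 40 | 91% | 1.5% | 94% | 96% | 0% | 93% |

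At sizes between these rows Wilson dips a little at p = 0.90 (92% with 5, 93% with 10). Clopper-Pearson is at least 97% in every cell of the table. At p = 0.90 the mean bootstrap width is 0.27 against 0.67 for the exact interval with 4 events, and 0.26 against 0.48 with 8.

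**Perfect classification.** The exact lower limit for m/m is 0.025^(1/m): 0.398 (m = 4), 0.541 (6), 0.631 (8), 0.832 (20). The bootstrap gives 1.00 to 1.00 in each case.

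**Specificity in the outcome ROC.** This rests on the favourable-outcome TB patients, 28 to 36 under the assumption above. At 28, 32 and 36 patients, coverage is 92%, 95% and 93% at specificity 0.80; 93%, 84% and 88% at 0.90; and 76%, 80% and 83% at 0.95.

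**LTBI controls, m = 20, if LTBI v TB is also analysed by ROC.** Coverage is 92%, 88% and 64% at specificity 0.80, 0.90 and 0.95.

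**AUC of a fixed marker.** Binormal simulation, 1,000 data sets, 500 stratified percentile resamples each. Coverage at true AUC 0.75, 0.85 and 0.95 is 86%, 82% and 76% with 4 events of 40; 92%, 88% and 81% with 8; 94%, 91% and 85% with 12; and 94%, 93% and 89% for 40 TB against 20 LTBI. If resampling is not stratified, a resample holds no event, and has no AUC, with probability (1 − 4/40)^40 = 1.5% at 4 events.

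**The case against.** **The event count is an assumption.** This stands. The composite includes culture conversion and is judged at each visit, so the unfavourable class at day 15 or month 2 could be much larger than 12. With 20 in the class, coverage is already 92% at sensitivity 0.80 and 95% at 0.70. The defect can only be stated as a range.

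**The 20 LTBI controls are not in the outcome ROC.** This stands. They have no value on the composite outcome of treated TB patients, and the paragraph on stage signatures does not mention the bootstrap. A reader might infer that the control group makes the main intervals collapse. The article does not support that; the controls matter only if a stage comparison is also analysed by ROC, and then mainly for specificity near 1.

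**The bootstrap variant is left open.** This stands in part. An analysis plan may name another type, stratify, or refit in each resample. If the cut-off is re-derived in every resample, the guaranteed 100% to 100% no longer follows automatically. More resamples or stratification do not cure it while the rule is fixed. For the AUC, another type could change the coverage, and the choice among intervals is partly preference.

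**This is a proof-of-concept study with its power limits admitted.** This stands as to severity. The Discussion concedes low power for the number of variables, and no go/no-go threshold is tied to these intervals. But admitting low power does not warn that an interval may miss its nominal level.

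**Optimism is the larger error.** Also true. Simulated pure-noise markers (28 or 58 candidates, at most 5 kept; assumed), selected, fitted and bootstrapped on the same patients, gave mean apparent AUCs of 0.79 to 0.94 with 4 to 12 events of 40. That is a separate fault, and curing it would not cure this one.

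**Conclusion.** The point holds in a limited form. The article fixes a bootstrap mean and interval for sensitivity and specificity. With a fixed rule, that interval has zero width for any perfectly classified class, and it under-covers when the class is small or accuracy is near 1. Under the assumed 4 to 12 events, coverage at true sensitivity 0.90 falls short of 95% by 24 points (12 events) to 61 points (4 events). At 0.80 the shortfall runs from 4 to 39 points. With 20 or more in the class and accuracy of 0.80 or less it is close to nominal.

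Two stronger statements are tempting. One is that the study's error bars are far too narrow; the article prints none, and the shortfall depends on an unstated class size. The other is that the intervals contain the truth only about half the time; this fits cells such as 6 to 8 events at 0.90 or 4 events at 0.80, not the plan as a whole. AUC under-coverage with few events is real but milder, and depends on the bootstrap type.

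The severity is should-fix. The conclusion rests on a 95% percentile interval, a fixed test rule and the assumed event range.

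**What to change.** Replace the sentence on bootstrap estimation with wording to this effect:

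- Sensitivity and specificity: report the observed (or optimism-corrected) value, not the bootstrap mean. Give the count x/m and a Wilson or Clopper-Pearson 95% interval.
- AUC of a fitted score: keep the bootstrap, stratify it by outcome class, and repeat marker selection and model fitting in each resample so that it corrects for optimism.
- AUC of a pre-specified marker such as RISK-6: a score or logit-scale interval is an acceptable alternative.
- If LTBI v TB is analysed by ROC, apply the same rules there.

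It would also help to state the expected number of unfavourable outcomes at each visit, so that the attainable precision can be seen beforehand.

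The cost is a short change of wording and standard R functions; no extra patients, samples or data are needed. The intervals become wider: with 4 events at true sensitivity 0.90, the mean width rises from 0.27 to 0.67 with the exact method.
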